## Background

The recommendations outlined in the latest guidelines published by the Surgical Infection Society (SIS) and the Infectious Disease Society of America (IDSA) regarding the proper duration of antibiotic therapy in patients with intra-abdominal infections are limited and non-specific According to these guidelines, an "antimicrobial therapy for established infections should be continued until resolution of clinical signs of infection occurs, including normalization of temperature and WBC count and return of gastrointestinal function" [1].

Such ambiguity is primarily attributable to the lack of clinical trials conducted on the topic of the optimal duration of antibiotic therapy.

These vague guidelines have manifested themselves in clinical practice; in most trials for antibiotic therapy, a fixed period ranging from 5 to 14 days is used for all patients presenting with community-acquired intra-abdominal infection, irrespective of severity of the peritonitis.

It should be noted that secondary peritonitis encompasses several different diseases and, as such, its severity has been known vary significantly [2].

It has been demonstrated that most patients enrolled in trials involving antibiotic treatment of IAI present with a mild form of the acute illness, which in 35-55% (and, in some studies, up to 70%) of cases is represented by acute appendicitis [3]. It should also be noted that many patients do not suffer from a fully developed and widely spread infection but rather experience a localized infection or simple contamination [4].

This means that many patients receive superfluous and unnecessary antibiotic treatments. Many non-random trials demonstrated that, by tailoring the duration of the antibiotic therapy to the extent of the infection as assessed during surgery, the same clinical results could be obtained in all groups of treated patients without the use of excessive antibiotic treatment regimens [5]. A recent systematic meta-analysis of twenty-eight studies on the duration of antibiotic therapy in cases of advanced pediatric appendicitis demonstrated that limiting the duration of antibiotic use to only 3 days was not associated with higher rates of intra-abdominal abscesses or wound infection [5].

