### Statistics

Each group will consist of 71 patients (142 patients for the entire study). All randomized patients (Intention to Treat Population) will be included in the analysis. Sample size has been calculated to reach a confidence level of 95% with a power of 80%. A sample size of 71 patients has been calculated assuming that Ertapenem can decrease the rate of "failure" from 30% to 10% as compared to AS.

The statistical analysis will be carried out using Epi Info 2000, Version 1.1 software package (Dean AG, Arner TG, Sangam S, Sunki GG, Friedman R, Lantinga M, Zubieta JC, Sullivan KM, Smith DC. Epi Info 2000, a database and statistics program for public health professionals for use with Windows 95, 98, NT, and 2000 computers; Centers for Disease Control and Prevention, Atlanta, Georgia, USA, 2000). The data generated in this study will be analyzed in two ways. Researchers will use the continuous numerical data to perform an analysis of variance (ANOVA), given that this method can discriminate between two continuous populations. Discrete data will be analyzed using the Chi-squared test or Fisher exact test, as appropriate. Differences between the two study groups will be considered statistically significant for p-values less than 0.05 (p < 0.05).

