### Surgical Intervention

Upon patient enrollment, the severity of the disease is evaluated by means of an APACHE II score and MPI prior to the operation. Diagnosis is based on the patient's clinical symptoms and intra-operative findings, including intra-operative cultures. The drug regimen being studied begins prior to surgery. The patients undergo surgery and then receive a 3-day treatment of either Ertapenem (1 g per day) or AS (3 g, 3× per day), depending on the assigned treatment group. Administration of the antibiotic therapy is then discontinued for those patients demonstrating an improved temperature (< 37.8°C), decreased WBC (returning to the normal range), and the presence of abdominal sounds by the third day of treatment.

In order to balance the treatment groups, the patients are stratified according to the site of infection; cases are either categorized under "complicated appendicitis" or they are filed under the all-encompassing group, "all other diagnoses." To limit the proportion of cases with complicated appendicitis, we have limited the enrollment into a stratum when almost 50% of cases are enrolled. Considering that an adequate surgical source control is a crucial factor determining the outcome of this disease, a blinded panel of three surgeons is asked to impartially assess the efficacy of the surgical procedure.

Aerobic and anaerobic cultures of intra-operatively retrieved specimens are obtained at baseline and processed in the clinical microbiology laboratories of the participating hospitals. All microorganisms are isolated, cultured, and tested for in vitro susceptibility to the study antibiotic by disk diffusion or microtiter dilution. Routine susceptibility testing of strict anaerobes is not required by treatment protocols.

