### Primary Endpoint

The study's primary endpoint is to compare the failure rates of shortened Ertapenem and AS antibiotic therapies in treating localized IAI.

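### Severity is scored at enrolment but plays no part in the primary failure test, which is valid and adequately powered yet forgoes a little power and protection against chance imbalance

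*Protocol article*

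**What the plan says.** The primary endpoint, under Primary Endpoint, is binary: "The study's primary endpoint is to compare the failure rates of shortened Ertapenem and AS antibiotic therapies in treating localized IAI". Statistics sizes the trial on a fall in failure "from 30% to 10% as compared to AS", with 71 patients per group, and gives one method for outcomes of this kind: "Discrete data will be analyzed using the Chi-squared test or Fisher exact test, as appropriate". No covariate, model or stratified test is mentioned.

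Surgical Intervention records severity at baseline: "Upon patient enrollment, the severity of the disease is evaluated by means of an APACHE II score and MPI prior to the operation". The same section balances the arms on site of infection only (complicated appendicitis against everything else) and gives neither score a role in allocation. The Background remarks that "secondary peritonitis encompasses several different diseases and, as such, its severity has been known vary significantly".

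**The concern.** The trial collects two pre-operative severity measures and then tests failure in a way that cannot use them. If severity predicts failure, two things follow.

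- Severity differences between patients stay in the error of the comparison, so power is lower than the same 142 patients could give.
- If the arms differ in severity by chance, the observed failure difference moves with that imbalance, and a 2x2 test cannot correct it. Deciding to adjust only after an imbalance has been seen would be data-driven, so the choice belongs in the plan.

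The article names the test, so this concerns a stated choice and not a detail left to an unseen analysis plan.

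**Working it through.** **Inputs from Statistics.** Failure 30% (AS) and 10% (Ertapenem); 71 per arm; significance at 0.05; power 80%. Sidedness is not stated. Two-sided is used because it alone reproduces the sample size.

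**Assumed input, not in the documents.** One normally distributed severity score, with log-odds of failure rising by 0, 0.5, 1.0 or 1.5 per SD (AUC about 0.50, 0.64, 0.74, 0.82).

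**1. The plan's own sample size.** Without correction:

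n = [1.96 × √(2 × 0.2 × 0.8) + 0.842 × √(0.3 × 0.7 + 0.1 × 0.9)]² / 0.2² = (1.109 + 0.461)² / 0.04 = 61.6, so 62.

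With continuity correction:

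(n/4) × [1 + √(1 + 4/(0.2n))]² = 15.4 × (1 + 1.151)² = 71.2, so 72 rounded up, against 71 stated.

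One-sided versions give 49 and 58. The stated figure is reproduced by the two-sided, continuity-corrected formula.

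**2. Power of the planned test.** Summing the binomial probabilities of all 2x2 tables with p < 0.05, at 71 per arm:

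- Chi-squared, uncorrected: 86.8%
- Chi-squared with Yates correction: 80.9%
- Fisher: 81.9%

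All meet the 80% target.

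**3. Power with the score in the model.** Simulation of 20,000 trials per row, with marginal rates held at 30% and 10%. Uncorrected Chi-squared is compared with a likelihood-ratio test for treatment from a logistic regression on treatment and score:

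| Log-odds per SD | Chi-squared | Adjusted | Gain (points) |
|---|---|---|---|
| 0 | 86.5% | 86.7% | about 0 |
| 0.5 | 86.4% | 87.6% | about 1 |
| 1.0 | 86.8% | 91.0% | about 4 |
| 1.5 | 86.9% | 93.9% | about 7 |

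At log-odds 1.0 the chance of missing the planned effect falls from 100 − 86.8 = 13.2% to 100 − 91.0 = 9.0%. With no true effect (20% in both arms) the rejection rate is 5.0 to 5.4% for Chi-squared and 5.3 to 5.6% for the adjusted test. The simulated model holds the score only; the site-of-infection stratum was not simulated.

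**4. Chance imbalance.** The between-arm difference in mean severity has SD √(2/71) = 0.168 score SDs. Hence P(|difference| > 0.25 SD) = 2[1 − Φ(0.25/0.168)] = 13.6%, and P(|difference| > 0.33 SD) = 4.9%. The effects of a 0.33 SD imbalance at log-odds 0.5, 1.0 and 1.5 are:

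- no true effect: the risk difference shifts by 2.5, 4.6 or 6.0 points;
- planned effect, Ertapenem arm sicker: the 20-point difference shrinks to about 17.6, 15.7 or 14.4 points.

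These figures ignore any balance gained from the stratum.

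**5. Room for a model.** Expected failures are 71 × 0.30 + 71 × 0.10 = 28.4. Treatment, one score and one stratum indicator are three terms, or 28.4/3 ≈ 9.5 failures per term. That supports one severity score but argues against entering both.

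**The case against.** The strongest reply is that nothing here is an error. The unadjusted test is valid under randomisation, its type I error is about 5%, and both named tests already exceed 80% power. That stands. A reader might infer that the planned test is wrong or the trial underpowered; the documents' own inputs show neither.

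A reader might also infer a gain of 8 to 10 points. Taking a severity-failure correlation of 0.5, Φ[(0.842 + 1.96)/√(1 − 0.25) − 1.96] lifts 80% to 90%, and the same formula lifts Fisher's 82% to 91%. This is not supported. No document gives that correlation, 80% is a design target and not the power of the uncorrected test, and the formula does not describe Fisher's test. Comparing the adjusted model with a Yates-corrected test also inflates the gap, because about 6 points of it come from the continuity correction. The comparison in step 3 is like for like.

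Entry is restricted to localised infection of mild to moderate severity, which narrows the spread of the scores. The Background sentence on variable severity describes secondary peritonitis as a whole and ties the variation to diagnosis, which is what the stratum partly captures. So it would be too strong to say that severity is left wholly unbalanced.

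Chance imbalance is already covered by the test's error rate. Even the 0.33 SD case moves the difference by less than one standard error, √(0.30/71) = 6.5 points. This limits the concern, but the imbalance would still go uncorrected in the trial at hand.

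Finally, the study drug also starts before surgery, and the article does not say that scoring comes before the first dose. That must be settled before a score is used as a baseline covariate.

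**Conclusion.** The point holds as a missed efficiency, not as a flaw in validity. Two severity scores are taken at enrolment, and the stated primary comparison uses neither. Adjustment would add about 0 to 7 points of power over the assumed range. The 1 to 4 points at log-odds 0.5 to 1.0 are the more likely gain, a judgement that rests on the mild-to-moderate entry criterion. Adjustment would also reduce sensitivity to a chance severity difference, and if the score is not prognostic it costs essentially nothing. The size depends on a severity-failure association that the documents do not give, on a two-sided test, and on the score being a true pre-treatment value. This is a worthwhile, low-cost improvement and not a necessary correction.

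**What to change.** In Statistics, pre-specify the primary analysis as a logistic regression of failure on treatment arm, with enrolment APACHE II as one continuous covariate and the site-of-infection stratum as a second term. Report the standardised (marginal) risk difference with a 95% CI. Keep the Chi-squared or Fisher test as the supporting unadjusted analysis, and repeat the model with MPI in place of APACHE II as a sensitivity analysis. State that the score used is the one recorded before the first study dose. Confirm that the named software can fit the model and produce the standardised difference, or name one that can.

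The cost is a short amendment to the analysis text. Both scores and the stratum are already planned, so no new measurements or patients are needed. The primary result would come from a model rather than a 2x2 table, and the few missing scores would need a simple baseline imputation rule.

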### Randomization

The randomization will be achieved by means of a computer-generated assignment system (a randomization algorithm). The results of this randomization will be sealed in numbered envelopes. Following the diagnosis of localized peritonitis, if the patient meets the inclusion criteria and if he/she is willing to participate in the study, the patient will sign a document verifying informed consent at which time the attending surgeon will disclose the contents sealed within the assigned envelope to determine the patient's randomly assigned treatment group.

The attending surgeon will then record the patient name and envelope number.

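### Patients are stratified by site of infection, but the primary failure rate is compared with an unstratified test, which is mildly conservative and gives up some precision

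*Protocol article*

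**What the plan says.** The Surgical Intervention section describes the stratification and its purpose: "In order to balance the treatment groups, the patients are stratified according to the site of infection". There are two strata, complicated appendicitis and everything else. The same section caps their size: "we have limited the enrollment into a stratum when almost 50% of cases are enrolled".

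The Primary Endpoint section makes the outcome a failure rate, which is binary: "The study's primary endpoint is to compare the failure rates of shortened Ertapenem and AS antibiotic therapies in treating localized IAI". The Statistics section names the test for such data: "Discrete data will be analyzed using the Chi-squared test or Fisher exact test, as appropriate". It sizes the trial at 71 per arm, "assuming that Ertapenem can decrease the rate of 'failure' from 30% to 10% as compared to AS", with 80% power and a 0.05 significance threshold.

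No section mentions a stratified or adjusted comparison. The Randomization section describes computer-generated allocation in sealed, numbered envelopes and does not mention the strata.

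**The concern.** Balancing the arms on a factor that predicts outcome removes that factor's contribution from the true sampling variance of the difference. A pooled Chi-squared or Fisher test still counts that contribution. Its standard error is therefore larger than the real one, and it rejects less often than its nominal level.

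The article itself treats site of infection as prognostic. The Background links the mild disease in earlier trials largely to appendicitis, and the protocol both stratifies on site and limits the share of appendicitis cases. At stake is part of the precision that the stratification was set up to provide.

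This is not simply a detail left to an unseen analysis plan. The article does name the test for binary data, and that test does not follow its own stratification.

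**Working it through.** **Inputs from the article.** 71 per arm, failure 30% (ampicillin-sulbactam, AS) versus 10% (Ertapenem), 5% level, 80% power, two strata capped near half.

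**Assumptions.** Two-sided testing (not stated); 36 and 35 patients per arm in the two strata; allocation balanced within strata; failure rates by stratum, which the article does not give.

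**Step 1: reproduce the sample size.** With mean rate 0.20:

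n = [1.96·√(2·0.20·0.80) + 0.8416·√(0.30·0.70 + 0.10·0.90)]² / 0.20² = (1.1087 + 0.4610)² / 0.04 = 61.6

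With continuity correction: (61.6/4)·[1 + √(1 + 4/(61.6·0.20))]² = 15.4·(2.151)² = 71.25.

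This is 72 rounded up and 71 rounded to nearest, so the stated figure reproduces. At 71 per arm, without strata, exact power is 86.8% (uncorrected Chi-squared), 80.9% (with Yates correction) and 81.9% (Fisher).

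**Step 2: standard error of the risk difference.** With arm rates P and Q, stratum rates p_i and q_i, n_i per arm in stratum i, and N = 71:

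- Pooled: SE_U = √{[P(1−P) + Q(1−Q)] / N}
- Stratified: SE_S = √{Σ n_i [p_i(1−p_i) + q_i(1−q_i)] / N²}

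Worked at the strong end, AS 10%/50% and Ertapenem 2%/18% (appendicitis/other):

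- P = (36·0.10 + 35·0.50)/71 = 0.297; Q = (36·0.02 + 35·0.18)/71 = 0.099
- SE_U = √[(0.2089 + 0.0891)/71] = 0.0648
- SE_S = √{[36·(0.09 + 0.0196) + 35·(0.25 + 0.1476)]/5041} = √(17.86/5041) = 0.0595
- Ratio = 1.088

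**Step 3: planned effect.** 400,000 simulated trials per row, both tests without continuity correction:

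| AS, app./other | Ertapenem, app./other | SE_U/SE_S | Power, Chi-squared | Power, CMH |
|---|---|---|---|---|
| 30/30% | 10/10% | 1.00 | 86.7% | 86.6% |
| 25/35% | 7/13% | 1.006 | 86.9% | 86.9% |
| 20/40% | 5/15% | 1.02 | 87.1% | 87.6% |
| 15/45% | 3/17% | 1.05 | 87.7% | 89.1% |
| 10/50% | 2/18% | 1.09 | 88.1% | 90.5% |

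In the last row, a nominal 95% interval built on SE_U covers 96.3%. With Yates correction the pooled test's power runs from 80.8% to 82.1% over these rows.

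**Step 4: no drug effect, 20% failure overall.** With equal strata the SE ratio is √{0.16 / mean of p_i(1−p_i)}:

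| Strata | SE ratio | Type I error, Chi-squared | Type I error, CMH |
|---|---|---|---|
| 15/25% | √(0.16/0.1575) = 1.008 | 4.9% | 5.0% |
| 10/30% | √(0.16/0.15) = 1.033 | 4.4% | 5.0% |
| 5/35% | √(0.16/0.1375) = 1.079 | 3.5% | 5.0% |

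If failure is the same in both strata (20/20%), Chi-squared rejects 5.1%. That small excess comes from the discreteness of the test, not from pooling. If overall failure under the null is 30% rather than 20%, the most extreme split tried (10/50%) gives 3.1% and an SE ratio of 1.11, again in the conservative direction.

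**The case against.** The strongest reply is that the design goal is already met. The error can only make the test stricter, and the stated tests keep power above 80% at 71 per arm. The loss is zero if site does not predict failure. That stands, and it makes this a modest gain in precision rather than a defect in validity.

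The conservatism also depends on balance within strata, and the Randomization section does not say how the envelopes carry the strata. Under unstratified allocation (200,000 simulated trials), the pooled Chi-squared rejects 5.2% at the 5%/35% null, so no level is lost. CMH still has more power: 87.5% against 86.7% at 20/40% on AS, and 90.2% against 86.9% at 10/50%. So the point about the level rests on the Surgical Intervention section alone, while the gain from stratifying the analysis does not.

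The stratum may also be known imperfectly, since treatment starts before surgery and diagnosis rests partly on operative findings. With 20% of labels wrong (an assumption), the gain in the extreme case shrinks to 87.8% against 87.2%, and the pooled test's null level is 4.5%.

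Finally, counts may be sparse. At 3% failure, 36·0.03 is about one expected failure in the Ertapenem appendicitis group. The fix therefore needs an exact fallback, as the current plan has.

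A reader might infer three stronger things that the article does not support:

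- **That the test fails its 5% level in a harmful way, or that the trial is underpowered.** Pooling only lowers the level, and power exceeds the target.
- **That pooling amounts to discarding about 14% of patients.** That is 1 − 0.1375/0.16, from an assumed sevenfold gap (5% versus 35%). At 10/30% the SE is only 3% too large.
- **That leaving out APACHE II is an error.** The article says only that "the severity of the disease is evaluated by means of an APACHE II score and MPI prior to the operation". An unadjusted randomised comparison remains valid, and covariate models are commonly left to an analysis plan.

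The Statistics section plans tests and p-values and mentions no intervals, so the standard error here describes the precision of the comparison, not a reported interval.

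**Conclusion.** The mismatch is real: the protocol stratifies on site of infection and then fixes a primary test that ignores it. The consequence is small and conservative. Over the assumed stratum rates around the planned effect, the standard error is about 0 to 9% too large and power about 0 to 2.4 points lower. The type I error is about 3.5 to 5% at 20% overall failure. Pooling does not inflate it, and power remains above 80%.

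These figures assume two-sided testing, near-equal strata, arms balanced within them, and a stratum that is correctly labelled and predicts failure. The last is implied by the protocol's choices but not quantified in it. The change is worth making because it costs almost nothing, not because the planned test is invalid.

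**What to change.** In Statistics, name the primary test separately from the general rule for discrete data:

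- Compare failure rates with a Cochran-Mantel-Haenszel test stratified by the site-of-infection stratum used at allocation. Use an exact stratified test where counts are sparse, with the criterion for sparseness fixed in advance.
- Report the Mantel-Haenszel risk difference with its 95% confidence interval.
- Keep Chi-squared or Fisher for the other discrete outcomes.

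In Randomization, say how the envelopes carry the strata, and have the stratum recorded with the envelope number so that the analysis uses the label in force at allocation. The article says only that patient name and envelope number are recorded.

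The cost is a few sentences and at most one extra recorded item. No patients or procedures are added, and 71 per arm stands. If site turns out not to predict failure, almost nothing is lost (86.6% against 86.7% power in the simulation).

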### Inclusion and Exclusion Criteria

#### Inclusion criteria

• Adult patients (>18 years of age)

• Patients requiring surgical intervention within 24 hours of diagnosis.

• Localized IAI (i.e., infection extending beyond the organ wall but confined by the closest hollow viscera, mild to moderate in severity):

• Acute appendicitis: Ruptured or perforated with abscess(es)

• Acute diverticulitis with perforation and/or abscess(es)

• Acute cholecystitis (including gangrenous cases) with either rupture or perforation

• Acute gastric and duodenal perforation (> 24 hours)

• Traumatic perforation of the intestines (> 12 hours)

• Secondary peritonitis due to perforated viscera

• Intra-abdominal abscess(es) (including those affecting both liver and spleen)

#### Exclusion criteria

• Traumatic bowel perforation requiring surgery within 12 hours

• Perforation of gastroduodenal ulcers requiring surgery within 24 hours

• Other intra-abdominal diseases in which the primary etiology was unlikely to be infectious.

• Patients lactating or pregnant

• Patients with history of allergy, hypersensitivity, or any severe reaction to the study antibiotics

• Patients with rapidly progressive or terminal illnesses;

• Patients with a history or presence of severe hepatic or renal disease (e.g. creatinine clearance < 0.5 ml/min/1.73 m2);

• Patients with a concomitant infection that would interfere with the evaluation of responses to the study antibiotics.

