### Data Collection

Patient data sheets are generated containing demographic figures as well as preoperative, operative, and postoperative information.

Upon enrollment, all patients undergo physical examinations and laboratory tests, (including a CBC with a WBC, differential analysis, platelet count, serum glucose assessment, BUN, and serum creatinine test). The same procedure is performed on the third day of the treatment regimen, at the end of the treatment cycle following the resolution of pathology, and during the post-treatment follow-up analysis (or more frequently as clinically relevant). Liver function studies, serum electrolytes, and urinalysis are performed upon the discontinuation of the intravenously administered antibiotic as well as periodically throughout the treatment process as clinically indicated. When clinically indicated during the course of antibiotic therapy, blood, urine and tissue specimens from clinically relevant intra-abdominal sites are obtained for culture and susceptibility testing. Such cultures are also performed at the end of antibiotic therapy, unless there is no material available for cultures and/or no clinical evidence of infection.

The clinical outcomes of eligible patients are classified in three groups: successful (no signs or symptoms of infection and no further need for antimicrobial therapy); failure (indicating no improvement, infection progression, or death due to infection); or late failure (indicating recurrence between cessation of antibiotic therapy and follow-up). Microbiological reports are recorded for each baseline pathogen. Favorable microbiological responses involve eradication of the pathogen(s), assessed on either a documented or presumptive basis (the latter occurring when there is no material available for culture in clinically recovered patients). By contrast, unfavorable microbiologic responses involve a chronic persistence of the pathogen(s), either on a documented or presumptive basis.

Any and all adverse events (AEs) that occur during the course of the study, beginning from the time of randomization, are carefully documented. These AEs are identified and described by the primary investigators.

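### The creatinine clearance printed as the example of severe renal disease, below 0.5 ml/min/1.73 m2, is a unit or decimal error

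*Protocol article*

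**What the plan says.** The Exclusion criteria of the protocol article rule out patients with past or current "severe hepatic or renal disease (e.g. creatinine clearance < 0.5 ml/min/1.73 m2". The number stands in parentheses as an illustration of the worded criterion. No other section gives a renal limit, a different unit or a correction.

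Three other statements bear on how the criterion is used:

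- Inclusion criteria: "Patients requiring surgical intervention within 24 hours of diagnosis".
- Surgical Intervention: "The drug regimen being studied begins prior to surgery". Patients then "receive a 3-day treatment of either Ertapenem (1 g per day) or AS (3 g, 3× per day", so the article states one dose per arm.
- Data Collection: the enrolment laboratory tests include "platelet count, serum glucose assessment, BUN, and serum creatinine test", so a renal measure is available at entry.

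**The concern.** An example in an eligibility criterion shows the recruiting surgeon where the word 'severe' begins. Here it places that boundary at a clearance so low that hardly any patient would fall below it, including patients whose kidneys are clearly failing.

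At stake are patient safety and consistent enrolment. Surgery follows diagnosis within a day, the study drug starts before the operation, and several departments recruit. A usable number would help the surgeons apply the criterion in the same way, and the printed one does not.

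**Working it through.** The plan does not derive its limit from other inputs, so there is no calculation to reproduce. The check is whether the printed value can describe severe renal disease.

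**Inputs**

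- Printed limit: 0.5 ml/min/1.73 m2 (Exclusion criteria).
- Normal clearance: 80 to 120 ml/min. This is an assumption, as the document gives no value.
- Three assumed adults for a cross-check: 30 years and 70 kg, 60 years and 70 kg, 80 years and 60 kg.

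**Step 1: volume cleared per day.** 0.5 ml/min × 1440 min = 720 ml.

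**Step 2: share of normal.** 0.5/120 = 0.42% and 0.5/80 = 0.63%. The result hardly depends on the assumed range: even with a normal value of only 50 ml/min, the share would be 0.5/50 = 1%.

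**Step 3: implied serum creatinine.** The Cockcroft-Gault formula (male form, not indexed to body surface), solved for creatinine in mg/dL, is (140 − age) × weight / (72 × clearance). At 0.5 ml/min the denominator is 36:

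- 30 years, 70 kg: 110 × 70/36 = 213.9
- 60 years, 70 kg: 80 × 70/36 = 155.6
- 80 years, 60 kg: 60 × 60/36 = 100.0

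Values of 100 to 214 mg/dL are not credible in a patient. The formula assumes a steady state, so this is only a plausibility check.

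**Step 4: what might have been meant.** Two kinds of slip give three candidate limits, all of them assumptions.

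| Candidate | Slip | Multiple of printed value | Share of assumed normal | Implied creatinine, mg/dL |
|---|---|---|---|---|
| 5 ml/min | decimal, one place | 5/0.5 = 10 | 4.2% to 6.3% | 10.0 to 21.4 |
| 30 ml/min | unit: 0.5 ml/s × 60 | 30/0.5 = 60 | 25% to 37.5% | 1.7 to 3.6 |
| 50 ml/min | decimal, two places | 50/0.5 = 100 | 41.7% to 62.5% | 1.0 to 2.1 |

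The shares are the candidate divided by 120 and by 80. The creatinine range applies the Step 3 formula to the same three adults. All three candidates lie above the printed value. Nothing in the document selects among them.

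**Step 5: reach into the statistics.** The Statistics section bases the sample size on failure rates of 30% and 10%, 95% confidence and 80% power. The renal limit enters neither that calculation nor the planned tests.

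**The case against.** The strongest reply is that almost nothing follows from the misprint. The words of the criterion decide eligibility and the number only illustrates them. Because the wording also covers a history of severe disease, known renal failure is excluded without any calculated clearance. A wrong but believable limit might mislead a surgeon, whereas a figure this extreme is likely to be seen as a misprint and ignored. This stands, and it keeps the point minor. It does not make the figure right, and the article offers no other number to fall back on.

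A second reply is that the article condenses a fuller protocol. That excuses omissions but not a value stated wrongly. It does mean that the absence of a named clearance equation, of a statement on indexing, or of eligibility-form detail is no fault of the article. Whether the full protocol or the form repeats the figure is not known.

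A fault in reading the PDF cannot be ruled out, but the sentence and its unit are intact and nothing suggests one.

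A reader might also infer more than the document supports:

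- **That the misprint makes patients with severe renal failure eligible.** It does not, because the worded exclusion remains in force.
- **That the printed figure is at least ten times below any plausible limit.** The factors of 10, 60 and 100 belong to three assumed candidates. The document does not say what was meant.
- **That the trial has no renal dose adjustment.** The article states one dose per arm, but a condensed article may leave adjustment rules to the full protocol.

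**Conclusion.** The concern holds as a minor error in an operative exclusion criterion. The printed figure cannot be the intended example of severe renal disease, and this conclusion is robust to any reasonable choice of normal clearance. The direction of the error is clear: the limit is too low. Its exact size is not, because the intended value and the kind of slip cannot be recovered from the document.

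The number of patients affected cannot be estimated either, and no route from the misprint to a wrongly enrolled patient is shown. A correction is still justified, because this is the sole numeric guide to renal eligibility.

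**What to change.** Replace the figure and its unit with the limit that the clinical leads confirm they intended. If 0.5 ml/s was meant, the text would read 30 ml/min/1.73 m2, but the leads must settle this and it should not be presumed. Keep severe renal disease as the operative wording, with the corrected number as its guide, and apply it using the serum creatinine already taken at enrolment.

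The cost is a one-line edit and no new laboratory test. At most a few patients with poor renal function would be more clearly excluded. If the leads settle on a limit as high as 50 ml/min, they should check that it still expresses 'severe', since it could exclude patients whom the present wording admits and would then change the criterion.
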